### Data collection

The study data collection process is outlined in Table 1.

**Table 1 Tab1:**
[figure not shown]
Treatment schedule and outcome measures

### Primary endpoint

Treatment success rate: If the following criteria are satisfied, treatment will be defined as successful:
In a patient with a fever and body temperature of 37.5 °C and abdominal pain requiring treatment at baseline, both fever relief within 3 days and elimination of abdominal pain within 4 days are confirmed.In a patient with abdominal pain requiring treatment, but who did not have baseline fever and body temperature ≥ 37.5 °C, disappearance of abdominal pain is observed within 4 days.

The definition of symptom change is as follows:
① Fever reliefFever relief is defined as the absence of fever with body temperature ≥ 37.5 °C without the use of antipyretic analgesics. Even when an antipyretic analgesic is used, if the body temperature of 37.5 °C or more does not occur even after 6 h after the administration of the antipyretic analgesic, it is determined that the patient has fever relief.② Elimination of abdominal painElimination of abdominal pain means that there is no abdominal pain without using antipyretic analgesics. Even when the antipyretic analgesic is used, it is determined that the abdominal pain has disappeared if no abdominal pain develops ≥ 6 h after the administration of the antipyretic analgesic. A visual analogue scale (VAS) score for pain should be obtained three times daily during the course of the abdominal pain.

### Secondary endpoints

The secondary endpoints are:
Number of hospital days: number of days until discharge, including the registration date, after trial registration.Change in inflammatory response (CRP, WBC, neutrophil count): Differences between the value at the time of registration (baseline value) of each measurement and the value at each measurement day.Thermal type: differences between the values at the time of registration (baseline value) of body temperature and the values on each measurement day.Number of days until oral ingestion: number of days until the beginning of oral intake, including the registration date, after trial registration.Recurrence rate (1-year follow-up observation): rate of recurrence at 1 year after randomization. Recurrence after discharge is regarded as diagnosis of colonic diverticulitis.Adverse events (types and frequency of side effects): side effects will be recorded for each observed adverse event, and the type and frequency will be determined.

### Statistical consideration

#### Sample size

Calculation of the sample size in this trial was based on treatment success rate. The treatment success rate using the same criteria was estimated from the results of our retrospective study and it is 75% in the patients treated with DBT and 50% without DBT. In our previous study the dropout rate was 2%, therefore in our study we will assume that we will have a 2% dropout. We use the method proposed by Fleiss et al. Based on this, a sample size of 170 patients (85 per arm) is required to provide the trial with 90% power to detect the superiority of experimental treatment over control, at a two-sided alpha level of 5%. The sample size is also identical to the tables in Fleiss: *Statistical methods for rates and proportions* [12].

### Statistical analysis

The treatment success rate will be compared between groups using the Pearson chi-square test. Time to confirmed treatment-success will be summarized using the Kaplan-Meier method. Continuous variables will be summarized as mean and standard deviation, and comparisons will be made using the unpaired Student’s *t* test. Categorical variables will be summarized as frequency and proportions, and comparisons will be made using the chi-square test. Two-sided *p* values <0.05 will be considered statistically significant.

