### Setting and participants

This study will be conducted in Japan. Patients will be recruited from the gastroenterology and surgery inpatient department at each of the hospitals in different districts in Japan. Participants who meet the following inclusion criteria are eligible:
Moderate to severe diverticulitis: diagnosis will be based on computed tomography (CT) evidence of diverticula-like structure, combined with tenderness or abdominal pain, thickening of the colon wall, signs of inflammation of pericolonic fat, tissue density, and vascular involvement. Pericolonic abscess, free air or extravasation, and accumulation of fluid will also be assessed to predict prognosis.Age at least 20 years and younger than 75 years.Ability to communicate with the investigators.Abdominal pain and/or fever with body temperature > 37.5 °C.Provision of written informed consent for participation after receiving sufficient explanation for participation in this study and achieving sufficient understanding.

Participants who meet the following exclusion criteria will not be enrolled:
Severe organ dysfunction as follows, based on blood tests within 4 the weeks before treatment starts:
Renal function: serum creatinine value 1.5-fold greater than the upper limit of the institutional standard.Liver function: serum aspartate aminotransferase (AST) value or serum alanine aminotransferase (ALT) threefold greater than the upper limit of the institutional standard.Central nervous function: encephalopathy or a patient suspected of having encephalopathy.Electrolytes: serum sodium < 125 mEq/L, serum potassium < 3.3 mEq/L.Highly likely to have abscess perforation due to malnutrition (albumin < 2.5 g/dL).Symptoms of obstructive ileus.Chronic anorexia, abdominal pain, and/or diarrhea symptoms before the onset of colorectal diverticulitis.Performance status (an indicator of general condition and the degree of restriction of the patient’s daily life) ≥ 3 before the onset of colorectal diverticulitis.History of DBT administration.Treatment with insulin preparations.Immunocompromised status.Pregnancy or postpartum status.Advanced allergy to Kampo formulas.

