### Randomization, allocation concealment, and blinding

Baseline measures will be obtained before randomization. The web-based online randomization system used in this trial was provided by an independent academic research organization at Kyoto Prefectural University of Medicine. In this registration method, the principal investigator or research coordinator accesses the URL of the Web registration system and registers himself, and obtains the allocation result. For registered case information, the information entered on the case report form (CRF) form is faxed to the data center. Allocation of subjects to each treatment group is performed using the central registration system. In this registration method, researchers access THE Web-based registration and randomization system, and obtain the allocation. Participants are randomized using a minimization method, in which the history of diverticulitis (initial or recurrent) and the severity (with abscess formation on CT and/or C-reactive protein (CRP) ≧ 10 or without abscess formation and CRP < 10) are used as adjustment factor [11]. Enrolled patients who provide informed consent will be randomized 1:1 in a blinded manner into either an experimental treatment group receiving a 10-day DBT regimen plus conventional therapy or a control group receiving a 10-day placebo regimen plus conventional therapy. Only the allocation number is written on the test drug box, and only the data center knows whether the box contains DBT or the placebo. Thus, all participants and treatment providers, those measuring the outcomes, and those who are to analyze the data will be blinded to treatment allocation.

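### Allocation is minimised on disease history and severity, but the primary Pearson chi-square ignores both, so if they predict success the test is mildly conservative and some precision is given up

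*Protocol article*

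**What the plan says.** **Allocation** (Protocol article, Randomization, allocation concealment, and blinding): "Participants are randomized using a minimization method, in which the history of diverticulitis (initial or recurrent) and the severity" (abscess on CT and/or CRP of at least 10, against neither) "are used as adjustment factor". Allocation is 1:1.

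**Primary test** (Statistical analysis): "The treatment success rate will be compared between groups using the Pearson chi-square test". No stratified or adjusted primary comparison is described. The only covariate work mentioned is at the end of the Discussion. There the authors are considering whether success correlates with antibiotics, BMI, gender, age and season. Neither minimisation factor is on that list.

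**Prognosis** (Setting and participants): "Pericolonic abscess, free air or extravasation, and accumulation of fluid will also be assessed to predict prognosis". So the article itself treats part of the severity factor as prognostic. It gives no strength for either factor.

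**Design figures** (Sample size): the success rate is taken from the retrospective study, where "it is 75% in the patients treated with DBT and 50% without DBT". The trial has 170 patients (85 per arm), for "90% power to detect the superiority of experimental treatment over control" "at a two-sided alpha level of 5" per cent, with 2% dropout assumed.

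**Endpoint** (Primary endpoint): febrile patients must meet a fever criterion and a pain criterion. A patient with pain "but who did not have baseline fever" must meet the pain criterion only.

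**The concern.** Minimisation holds the arms close together on the two factors, so the part of the variation in success that the factors explain can no longer fall unevenly between arms. The Pearson variance is built for simple randomisation and still counts that part. If the factors matter, the standard error is larger than the real sampling error of the difference. The test then rejects less often than 5% under the null, and a matching confidence interval is wider than it need be. Some power that the balanced design has already paid for is not used.

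The stake is efficiency. The planning rates come from a retrospective open-label study with 11 treated and 23 untreated patients. The true effect may therefore be smaller than planned, and forgone precision would then matter more.

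**Working it through.** **1. The plan's own sample size.** Inputs from Sample size: 0.75 and 0.50, two-sided 5%, power 90%. The mean rate is 0.625.

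- Fleiss without continuity correction: n' = [1.960·√(2·0.625·0.375) + 1.282·√(0.75·0.25 + 0.50·0.50)]² / 0.25² = (1.342 + 0.848)² / 0.0625 = 76.7, so 77 per arm.
- With continuity correction: n = (n'/4)·[1 + √(1 + 4/(n'·0.25))]² = 19.18 × 2.099² = 84.5, so **85 per arm, 170 in all**. The stated figure is reproduced.
- Power of the uncorrected Pearson test at 85 per arm: Φ[(0.25·√85 − 1.342)/0.661] = Φ(1.456) = 92.7%. At 83 per arm (about 2% lost) it is 92.1%.

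So the Pearson test, run without a continuity correction, starts about 2 to 3 points above 90%.

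**2. What balancing does to the variance.** The Pearson null variance is p̄(1−p̄)(1/n₁+1/n₀). At p̄ = 0.5 the standard error is √(0.25 × 2/85) = 0.0767. With the factor cells balanced, the true variance is approximately [p̄(1−p̄) − V](1/n₁+1/n₀), where V is the variance of the success probability between cells. If V = 0 the two agree. If V > 0 the Pearson standard error is too large.

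**3. Size of the effect.** This needs assumptions that the article does not supply: factor prevalences of 30% and 50%, a biased coin of 0.8, and an odds ratio for treatment failure that is the same for each factor. There were 20,000 simulated trials per row (simulation error about 0.15 to 0.2 points). CMH is the Cochran-Mantel-Haenszel test over the four factor cells.

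Under the null, N = 170:

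| Odds ratio per factor | Pearson SE | True SE | Ratio | Pearson type I error | CMH type I error |
|---|---|---|---|---|---|
| 1.5 | 0.0765 | 0.0762 | 1.00 | 5.5% | 5.2% |
| 2 | 0.0765 | 0.0748 | 1.02 | 4.9% | 5.1% |
| 3 | 0.0765 | 0.0721 | 1.06 | 4.2% | 5.0% |
| 5 | 0.0765 | 0.0687 | 1.11 | 3.2% | 5.1% |

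The 5.5% in the first row reflects the discreteness of a 2×2 table with near-equal arms. Deterministic minimisation gives much the same picture (3.1% at an odds ratio of 5).

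Power at the planned 75% versus 50%:

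| Odds ratio per factor | N = 170: Pearson / CMH | N = 166: Pearson / CMH |
|---|---|---|
| 1.5 | 93.0% / 93.0% | 92.2% / 92.2% |
| 2 | 93.1% / 93.6% | 92.6% / 93.3% |
| 3 | 94.1% / 95.3% | 93.1% / 94.6% |
| 5 | 94.7% / 96.5% | 93.9% / 96.3% |

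The gain is about 0 to 2.5 points. Even where neither factor matters (odds ratio 1), Pearson has 92.5% at N = 170 and 92.0% at N = 166, and stratifying costs at most about 0.2 points.

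**4. Unequal factors, fever, and a smaller effect.** A second model assumes prevalences of 50% severe, 30% recurrent and 50% febrile, with odds ratios for success given in the order severity/history/fever. The effect of 70% versus 50% is an assumption, not a protocol figure. Ranges span repeated runs.

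| Odds ratios | Pearson type I error | Power, 75% v 50%: Pearson / CMH two factors / plus fever | Power, 70% v 50%: Pearson / CMH |
|---|---|---|---|
| 0.25/0.67/0.5 | 4.2–4.3% | 93.6% / 94.8% / 94.9% | 76.8–78.3% / 79.6–80.9% |
| 0.17/0.5/0.25 | 3.6–3.8% | 93.7% / 95.3% / 96.2% | 77.8–78.3% / 81.7–82.3% (two factors), 84.4–84.7% (plus fever) |
| 0.5/1/0.5 | about 5% | 93.4% / 93.6% / 93.5% | no meaningful difference |

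At 70% versus 50%, stratifying by the two factors adds about 0 to 4 points (82.3 − 78.3 = 4.0 at most).

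**The case against.** The strongest defence is that nothing the trial promised is lost. The unadjusted test matches the two-proportion sample size. Its error is on the safe side, the crude difference still estimates the marginal effect, and its power exceeds 90% in every scenario at the planned rates. The loss is also conditional: no prognostic strength is given, nothing in the article says that recurrent disease predicts four-day success, and weak factors cost nothing. All of this stands, and it sets the size of the point. What it does not remove is the mismatch between the stated allocation and the stated test.

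A reader might infer three stronger things that the article does not support.

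- **That power falls short, for example to about 78%.** That figure belongs to 70% versus 50%, which is not the planned effect. It is mainly the price of the smaller effect, not of the test.
- **That baseline fever strongly determines success.** The extra criterion means that, for the same pain course, a febrile patient can only have an equal or lower chance of success. If most patients who are pain-free by day 4 have already lost their fever, the criterion changes little. The article gives no rate.
- **That chance imbalance in fever is a fault of the Pearson test.** Fever is not a minimisation factor, so its chance imbalance is already covered by the Pearson standard error. Leaving it out causes neither bias nor excess type I error.

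**Conclusion.** The point holds as a minor one. The allocation scheme and the primary test do not match. If the minimisation factors predict success, the Pearson test is mildly conservative: type I error about 3% to 4.5% under assumed strong factors, about 5% under weak ones. At the planned effect, stratifying adds about 0 to 2.5 points to a power that already exceeds 90%. At 70% versus 50%, it adds about 0 to 4 points. A significant Pearson result remains valid.

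The direction follows from the design and needs only that the factors be prognostic, which the article implies for abscess alone. The size rests on assumed prevalences, odds ratios and coin probability.

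**What to change.** Before unblinding, state that the primary comparison is a Cochran-Mantel-Haenszel test stratified by history (initial or recurrent) and severity as defined for allocation. Report it with a Mantel-Haenszel risk difference and 95% confidence interval, and keep the Pearson test as a supportive analysis. Name this one method only. A logistic model with a standardised risk difference is a different analysis with different weights, and offering both would leave the primary analysis open.

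Baseline fever (yes/no) may be added as a pre-specified stratifier for precision. This is optional, and its benefit depends on a prognostic strength that is not known.

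The cost is wording only. Both factors are captured at allocation, and baseline fever is needed to apply the endpoint. No new data and no larger sample are required.

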### Quality control and trial management

The management structure comprises the principle investigator (PI), a trial management group, and a data monitoring committee. The trial management group is responsible for conducting the trial and will meet monthly to discuss trial progress. The PI will visit each collaborative hospital for face-to-face meetings and sharing of information to promote patient recruitment. The data monitoring committee will review interim safety data and periodically review the conduct of the study. Additionally, all data will be monitored centrally every month. In this study, interim analysis of efficacy is not planned. Final analysis will be performed by the data center and our statistician. Additional monitoring may be performed at the discretion of the monitoring manager. The data monitoring committee has met once prior to the start of patient recruitment. At least twice per year, participating investigators, research assistants, and research nurses will be required to attend a training workshop for clinical research to ensure strict adherence to the study protocol and familiarity with the trial administration process. The data collected in this trial will comprise information recorded in case report forms and questionnaires. Data quality will be checked regularly by research assistants and overseen by monitors; all modifications will be marked on the case report forms, and data managers will recheck the data before they are officially logged. The database will be locked after all data have been cleaned. If participants withdraw from the trial during the study period, the reasons will be documented, and the dropout rate will be statistically analyzed.

## Discussion

The main purpose of this study is to assess the treatment effect of DBT in moderate to severe acute diverticulitis. The secondary aim of this study is to investigate the preventive effect of DBT in colonic diverticulitis. Patients with a history of diverticulitis are advised to consume a high-fiber diet or ingest fiber supplements, minimize red meat consumption, avoid non-aspirin non-steroidal anti-inflammatory drugs, stop smoking, maintain or achieve a healthy body weight, and exercise regularly [6]. Although multiple studies have investigated the methods of colonic diverticulitis prevention, the existing results are not supported by high-quality evidence. In this study, we will investigate differences between treatment with DBT combined with antibiotics, relative to treatment with placebo.

Diverticula can occur at any site in the colon. However, in Western countries they occur primarily in the sigmoid colon; in contrast, in Japan the right side of the colon or both sides of the colon are more commonly involved. The standard treatment for acute uncomplicated diverticulitis has been bowel rest (i.e., fasting), intravenous fluids, and intravenous antibiotics. There will be a diverse assortment of antibiotics used in this study, based on variability in the antibiotics used in clinical practice among the centers participating in the study. Additionally, while many trials have focused on surgical treatment of acute diverticulitis, there have been few studies dedicated to medical treatment of this condition. A review of the published data revealed that there is no standardization of the medical treatment of uncomplicated acute diverticulitis [13]. In this study, we will not limit the the types of antibiotics used; all antibiotics administered will be noted in the case report forms.

In Kampo medicine, internal abscesses generally comprise abscesses of the lungs and intestines. Similar to external abscesses, they are attributed to heat and constraint, which allow the formation of toxins and secondarily lead to the formation of pus. The appropriate strategy is to discharge the toxin, eliminate the phlegm, clear the heat, and open the constraint. If clumping of heat with stasis and stagnation is also present, herbs such as *Rhei Radix et Rhizoma* (*da hung*大黄) and *Moutan Cortex* (*mu dan pi*牡丹皮) can be added to drain heat and dispel stasis [8]. In this context, DBT is one of the most suitable formulas for treatment of acute diverticulitis. DBT might have preventive effects on the recurrence of diverticulitis, although the prognosis of patients was not reported in a prior study [9].

Most herbal medicine is orally administered, and many components of these medicines come into contact with the intestinal microflora in the alimentary tract. Some are modified by intestinal bacteria before their absorption into the bloodstream from the gastrointestinal tract [14]. Although administration of intravenous antibiotics may influence intestinal microflora and the effect of DBT might be altered, compared with classical therapy, our previous study showed that both intravenous antibiotics and DBT could be used at the same time [9].

DBT consists of five crude drugs: *Rhei rhizoma*, *Natrium sulfuricum, Moutan cortex, Persicae semen,* and *Benincasae semen*. Of these, *Rhei rhizoma* or rhubarb is one of the most important traditional herbal medicines, widely used in Kampo and traditional Chinese medicines for thousands of years, especially as a purgative. It might prevent bowel retention, overgrowth of toxic bacteria in patients with acute diverticulitis, and enable resolution of acute inflammation.

Studies of other functions of rhubarb in modern medical research in both clinical and basic science settings have revealed that rhubarb has multiple effects, including defervescence, anti-inflammatory actions, and expulsion of a variety of harmful materials (e.g., endogenous and exogenous toxins) from the bowel and the body.

It is shown that emodine in *Rhei rhizoma* protects against acute lung injury induced by lipopolysaccharide, and that its administration improves respiratory function [15]. These effects may be related to the reduction of inflammation in diverticulitis.

*Moutan cortex*, the root cortex of *Paeonia suffraticosa*, is an herbal medicine widely used as an analgesic, antispasmodic, and anti-inflammatory agent. *Moutan cortex* reportedly inhibits the secretions of interleukin-8, a major mediator of acute neutrophil-mediated inflammation, and macrophage chemoattractant protein-1, a potent mediator of chronic macrophage-mediated inflammation in human monocytic U937 cells [16]. Recently, *Moutan cortex* was shown to protect against sepsis induced by lipopolysaccharide/D-galactosamine [17]. The known chemical components of *Moutan cortex* include paeonol, paeonoside, paeonolide, paeoniflorin, benzoylpaeoniflorin, oxypaeoniflorin, benzoyloxy-paeoniflorin, and apiopaeonoside.

*Moutan cortex* inhibits the lipopolysaccharide plus interferon-γ induced expression of inducible nitric oxide synthase and tumor necrosis factor-α release. The lipopolysaccharide plus interferon-γ induced activation of nuclear factor-κB is almost entirely blocked by *Moutan cortex* [18].

*Persicae semen* or *Prunus persica*, is also well-known as a traditional medicine in Japan, China, and other Asian countries. It is frequently used as an ingredient in a variety of Kampo and Chinese medicine formulas, particularly those used to treat women’s diseases. The chemical constituents of the herb include cyanogenic glycosides, amygdalin, and prunasin as major components, along with glycerides, sterols, and emulsion. Amygdalin is abundant in the seeds of bitter almond and apricots of the *Prunus* genus, and other rosaceous plants. *Persicae semen* has anti-edema, anti-writhing, and anti-inflammation activities.

Each of these crude drugs has some anti-inflammatory effects, and the combination of these crude drugs may produce the synergy of Kampo medicine. Moreover, we are considering testing for correlation between the incidence of diverticulitis and body mass index (BMI), gender, age, and season, and between the success rate in treating diverticulitis and antibiotics, BMI, gender, age, and season.

In conclusion, this study protocol may contribute to the development of an effective treatment to help relieve acute diverticulitis. It may also provide evidence on the efficacy and safety of DBT in patients with acute diverticulitis.

